## Abstract

**Background:**

Endometrial cancer survivors comprise a high-risk group for obesity-related comorbidities. Healthy eating and physical activity can lead to better health and well-being, but this population may experience difficulties adopting healthy lifestyle practices. Personalised behaviour change programmes that are feasible, acceptable and cost-effective are needed. The aim of this trial is to pilot a manualised programme about healthy eating and physical activity.

**Methods/design:**

This is a phase II, individually randomized, parallel, controlled, two-site, pilot clinical trial. Adult endometrial cancer survivors (n = 64) who have been diagnosed with endometrial cancer within the previous 3 years and are not on active treatment will be invited to participate. Participants will be assigned in a 1:1 ratio through minimisation to either an 8-week, group-based, behaviour-change programme with weekly 90-min sessions about healthy eating and physical activity or usual care. The intervention will focus on self-monitoring, goal setting and self-rewards. Follow-up assessments will be conducted at 8 and 24 weeks from the baseline assessment. Primary feasibility outcomes will include rates of recruitment, adherence, and retention.

**Discussion:**

The study results will inform the development of a definitive randomised controlled trial to test if the programme can improve the health and quality of life of this population. It will also provide guidance on costing the intervention and the health care resource use in this population.

**Trial Registration:**

ClinicalTrials.gov identifier: NCT02433080, 20 April 2015.

**Electronic supplementary material:**

The online version of this article (doi:10.1186/s13063-016-1260-1) contains supplementary material, which is available to authorized users.

## Background

Endometrial cancer is the most common gynaecological cancer in developed countries, with more than 75 % of the patients surviving for at least 5 years [1]. Low physical activity, poor diet and obesity are risk factors for the development of endometrial cancer [2]. These factors may also be linked with quality of life after cancer treatment [3]. While the evidence on the impact of post-diagnosis health behaviours on endometrial cancer survival is still unclear [4], evidence from other cancer sites suggests that similar factors that affect cancer development may also influence survival [5–8]. However, adherence to lifestyle recommendations [9] is limited [10], putting survivors at high risk for other chronic diseases.

Cancer survivors often report making health behaviour changes [11]. As survivors might be motivated to practice health-protecting behaviours, a cancer diagnosis has been posited to be a ‘teachable moment’. However, survivors rarely initiate lifestyle behavioural changes [12–15]. Behaviour change interventions capitalising on the ‘teachable moment’ might therefore be more effective than those targeting the general population [16, 17]. While the optimal timing of the teachable moment has not been defined, the post-treatment period seems optimal for the provision of healthy eating interventions [18]. Promotion of physical activity might be independent of timing [18], but 10 physical activity trials have accrued survivors within a median of 3.1 years after their diagnosis [19]. However, willingness to participate in health behaviour trials reduces with time since diagnosis in long-term cancer survivors (>5 years since diagnosis) [20]. Qualitative data in endometrial cancer survivors also support the post-treatment period as the most appropriate time to intervene [[name] et al: Attitudes, challenges, and needs about diet and physical activity in endometrial cancer survivors: a qualitative study. Submitted]. While in a vital position to do so, health professionals do not tend to provide lifestyle advice [21], particularly given time constraints. Therefore, feasible and effective interventions are needed to promote implementation of lifestyle recommendations.

### Rationale

Theory-based behaviour change interventions suggest that improving diet and physical activity is safe, acceptable and feasible with promising effects on both psychological and physiological outcomes, including quality of life [22–25]. In the United States, the two interventions in endometrial cancer survivors have also shown sustained changes in behavioural outcomes and indicated potential changes in quality of life domains [26—27]. Quality of life and its components are valuable outcome measures, as they are associated with disease status and the presence of co-morbidities, and they are core components of strategic needs assessments for cancer survivors [28]. However, the majority of these interventions lasted for 6 months or more and were resource intensive (for example, personalised materials, highly trained coaches). Although cost-effective analyses are scarce [29], such intensity or duration may render them inappropriate for wide dissemination. Furthermore, these interventions may not be fully applicable to other cancer groups given the differences between long-term treatment effects. Qualitative work with endometrial cancer survivors suggests they highly desire information regarding specific late-treatment effects and advice on healthy eating and physical activity post-treatment and in person [[name] et al: Attitudes, challenges, and needs about diet and physical activity in endometrial cancer survivors: a qualitative study. Submitted]. Finally, similarities in effectiveness of programs delivered across developed countries are expected. However, both the health systems and the causes of obesity differ between the USA and the United Kingdom [30]. Despite the common focus of such programs on healthy eating and physical activity, these differences might make a program developed in one context less applicable in the other.

A need exists, therefore, to develop effective behaviour change interventions for endometrial cancer survivors that meet an identified need and can be implemented in the cancer care pathway both in terms of length of programme and resource use. Pre-existing programmes for improving diet and physical activity in the general population, which have demonstrated usability within the National Health Service (NHS), may be an untapped resource. These programmes could be adapted to take into account the specific needs and experiences of endometrial cancer survivors while retaining the core components that have made them effective in other populations.

### Aim

The aim of this pilot study is to assess the feasibility of a manualised healthy eating and physical activity programme in endometrial cancer survivors post active treatment.

The main research question is as follows: ‘Is it feasible to design a randomised controlled trial that will assess if the *Shape-up following cancer treatment* programme is more effective than usual care in improving the health-related quality of life of endometrial cancer survivors?’

### Study objectives

#### Primary research objective

The primary research objective is to assess the feasibility of the overall trial procedures.

#### Secondary research objectives

Secondary research objectives are to accomplish the following: (1) to obtain variance estimates for clinical outcome measures to be used in the large-scale RCT that will inform the measurement of the primary outcome for the larger trial and, subsequently, the sample size calculation; (2) to assess willingness of the clinical staff to recruit participants; (3) to assess willingness of eligible participants to be randomised; (4) to examine potential adverse effects of the intervention; (5) to perform a basic economic analysis with the aim to inform the larger trial; (6) to assess reasons for loss to follow-up; and (7) to access the overall acceptability of the intervention.

## Methods/design

The protocol has been prepared according to Standard Protocol Items: Recommendations for Interventional Trials (SPIRIT) [31] and Template for Intervention Description and Replication (TIDieR) guidelines [32]. For completed checklists, see Additional files 1 and 2.

### Preliminary work

The intervention is based on *Shape-up: a lifestyle programme to manage your weight,* an 8-week weight management programme, which aims to help service users learn new behaviours and manage their weight [33, 34]. This manualised healthy lifestyle programme is based on social cognitive theory [35] and control theory [36] and focuses on self-control, self-efficacy, and behavioural relapse prevention. The intervention is under the tier 2 weight management services [37] and in line with NICE guidance on lifestyle weight management services [17] and individual approaches in behaviour change [38]. Currently, a version of original program is successfully being run in two London boroughs as part of the local joint strategic needs assessment [39].

The programme has been renamed (*Shape-up following cancer treatment: a self-help guide to eating well and being active*), and the intervention development process will be separately reported. In brief, the tailored version is focused on healthy eating and physical activity rather than weight loss, a focus based on the lack of strong evidence for the benefits of intentional weight loss in cancer survival outcomes. A stronger focus on resistance, flexibility and balance exercises has been be added, given their benefits in cancer survivors [40, 41]. Furthermore, specific recommendations about radiotherapy and chemotherapy treatment effects have been added to the booklet, such as avoiding high-fat foods or choosing cooked vegetables.

### Study design

The DEUS pilot trial is an 8-week, two-arm, individually randomised, controlled pilot trial comparing the use of the *Shape-up following cancer treatment* programme to usual care. According to MRC guidance for complex interventions [42], this is a Phase 2 feasibility study. Randomisation will be performed with minimisation, using a 1:1 allocation.

### Study setting

Participants will be recruited from two major academic hospitals in London with sufficient caseload of endometrial cancer patients; University College London Hospitals NHS Foundation Trust, and Barts Health NHS Foundation Trust. The intervention program will be delivered at the University College Hospital Macmillan Cancer Support and Information Centre, located in central London.

### Selection of subjects

#### Inclusion criteria

Women aged > 18 years (no upper age limit) who have been diagnosed with endometrial cancer (ICD C54.1) within the previous 36 months will be eligible to take part in the study. They must also be able to understand spoken and written English. The cut-off of 36 months was chosen to account for the duration of treatment and allow for a sufficient pool of survivors for recruitment, so the presence of the teachable moment and the elimination of early major treatment effects can be balanced.

#### Exclusion criteria

Women who meet at least one of the following criteria will be excluded: (1) diagnosed with stage IVB (metastatic) endometrial cancer (any metastasis beyond the pelvis); (2) undergoing active anticancer, and/or palliative treatment; (3) having a second primary cancer; (4) lacking the mental capacity to decide to take part in the study and to participate in it (based on the clinical team’s judgement in accordance with the Mental Capacity Act 2005 Code of Practice 2007); (5) having severe depression (consultant’s judgement based on the DSM-IV criteria); (6) unavailable for longitudinal follow-up assessments; (7) having participated in a professionally delivered weight loss or exercise program during the previous 6 months; (8) having a WHO performance score 3-4 [43]. These criteria comply with all but the disability category in the NICE Equality Impact Assessment for lifestyle weight management services [17].

		Discussion about previous experience of diet and physical activity changes, how cancer has shaped their eating and activity patterns, and hopes and fears about the programme	15 min
		Motivation for change	10 min
		Break	5 min
		Setting a lifestyle target	10 min
		Information and discussion about the importance of self-monitoring and food diaries	10 min
		Round-up and preparation for next session	5 min
		Take-home message	5 min
Session 2	Keeping to a regular eating pattern	Review: Discussion about self-monitoring and food diaries and goal progress	
		Volunteer-led discussion: Keeping to a regular eating pattern	
		Key learning points: The importance of keeping to a regular eating pattern, the definition of a regular eating pattern, the importance of breakfast, suggestions for goals, and disadvantages of eating regularly.	
		New topic: Goals and rewards	
		Discussion about the principles of goal-setting, group exercise about setting SMART goals, exercise about goal planning, discussion about rewards, and group exercise about non-food rewards	
		Round-up and preparation for next session	
		Take-home message	
Session 3	Physical activity	Review: Discussion about keeping a diary, setting a regular eating goal, goal-setting, rewards, and goal progress	20 min
		Volunteer-led discussion: Physical activity	30 min
		Key learning points: The importance of physical activity for health and wellbeing, the difference between physical activity and exercise, goals to aim for (30 min of moderate physical activity per day and muscle fitness exercises twice a week), and the importance of incremental increase in physical activity levels.	
		Break	10 min
		Setting an activity goal: individual exercise to help them focus on what they need to think about in order to improve their activity levels and group exercise for improving goal-setting skills	15 min
		Round-up, and preparation for next session	10 min
		Take-home message	5 min
Session 4	Eating a balanced diet	Review: Discussion about last week’s topics and creating a physical activity goal and goal progress	20 min
		Volunteer-led discussion: Getting a healthier balance of foods.	30 min
		Key learning points: the five food groups, choosing which foods to make (plenty of whole grains, fruits, and vegetables; moderate amounts from the ‘meat, fish and alternatives’ and ‘milk and dairy’ groups, preferably low-fat; have little amounts of ‘foods high in fat or sugar’ and prefer healthy oils; limit processed meat, and sugary and alcoholic drinks; prefer foods low in salt).	
		Break	5 min
		New topic: Lapses	25 min
		Information, group exercise, and discussion on how to deal with lapses	
		Round-up, and preparation for next session	5 min
		Take-home message	5 min
Session 5	Keeping an eye on food serving sizes	Review: Discussion about last week’s topics, goal progress, and exercise about managing lapses	20 min
		Volunteer-led discussion: Keeping an eye on food serving sizes	50 min
		Key learning points: Each participant brings a weighed portion of some foods, and group members discuss understanding food serving sizes and how many servings they should aim for (the food servings reflect a 2,000 kcal diet for women).	
		Break	10 min
		Round-up and preparation for next session	5 min
		Take-home message	5 min
Session 6	External triggers	Review: Discussion about last week’s topics and goal progress	20 min
		Volunteer-led discussion: External triggers	35 min
		Key learning points: The difference between external and internal triggers, and main strategies for dealing with external triggers	
		Break	5 min
		New topic: Internal triggers	20 min
		Discussion about hunger and cravings, group exercise for the dealing with cravings and the difference between craving and hunger and discussion about fatigue	
		Round-up and preparation for next session	5 min
		Take-home message	5 min
Session 7	Internal triggers	Review: Discussion about last week’s topics, goal progress, and feelings about the group coming to an end	20 min
		Volunteer-led discussion: Internal triggers	40 min
		Key learning points: Definition of internal triggers (hunger, cravings, fatigue, emotions, and unhelpful thoughts) and strategies to deal with those	
		Break	5 min
		New topic: Lapse chains	10 min
		Information about lapse chains and group exercise of putting together a behaviour chain	
		Round-up, and preparation for next session	10 min
		Take-home message	5 min
Session 8	Food labels and the *Shape-up* change plan	Review: Discussion about last week’s topics and goal progress and reviewing earlier areas of the programme	10 min
		Volunteer-led discussion: Food labels	30 min
		Key learning points: The ingredient list and the various names of sugar and saturated fat in food labels, the importance of checking the sugar, saturated fat, and salt content in the labels, and tips for smart shopping	
		Break	5 min
		New topic: The *Shape-up* change plan	20 min
		Information about how to complete a *Shape-up* change plan and individual exercise on filling a mock plan	
		Discussion: Group members discuss their change plan, they re-evaluate their lifestyle target from Session 1, and are given information about the importance of continuing with self-monitoring	20 min
		Round-up, and maintaining changes for the long term	5 min
		Take-home message	5 min

Those who miss sessions will receive standardized e-mails or mail with the content of the session. They will also be asked not to discuss the intervention with fellow patients in an attempt to minimize contamination and avoid leakage of intervention details among patients in the study arms.

### Control group

Participants in the control group will be offered usual care. Quantifying usual care is challenging, but our preliminary qualitative study suggested that lifestyle advice is limited in the current clinical setting [[name] et al Attitudes, challenges, and needs about diet and physical activity in endometrial cancer survivors: a qualitative study. Submitted]. During the trial, participants will only be contacted for the assessments. After the final follow-up, the researcher will have a 5-minute discussion with them using a standard statement focusing on the link between lifestyle and health consequences and targeting their motivation to improve their health. At that point, they will also receive the ‘Healthy living after cancer’ booklet, a brief self-help manual produced by the World Cancer Research Fund [45].

### Outcome measures

#### Primary outcome measures

The primary outcome measures for the pilot trial are as follows:The recruitment rate.The adherence rate (attendance of the sessions).The retention rate (complete follow-up).

The main criterion to judge the pilot study successful and a large-scale RCT feasible using the recruitment measure is recruiting (consenting) 30 % of the eligible participants (32 participants per 110 estimated to be eligible in each centre during the 6-month recruitment). This target seems reasonable based on our previous experience and similar rates indicated in the literature [46, 47]. The primary measure to be used in the large-scale RCT is projected to be a change in global quality of life as measured by the EORTC Quality of Life Questionnaire (QLQ-C-30). However, the choice of additional primary outcomes will be finalised after taking into account the results of the feasibility study.

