### Sample size

Although this is a feasibility study, a sample size has been specified for examining the recruitment rate, using A’Hern’s approach for one-stage phase II trials [48]. Regarding recruitment, a success rate of approximately 30 % or more would be desirable for the trial to be considered feasible. A success rate of 15 % or less would be unacceptable. The trial will test the null hypothesis H_0_ that recruitment is ≤ 15 % against the alternative hypothesis H_1_ that recruitment is ≥ 30 %. With a 5 % level of significance and 90 % power, 64 participants are needed so that we can estimate whether the percentage of participants with successful recruitment is ≤ 15 % or ≥ 30 %. If we can recruit 15 or more participants, we can reject the null hypothesis.

A trial of 64 (32 per arm) will be sufficient to test the above hypothesis and allow decisions to proceed to a Phase III trial. It will also allow for rich feedback from the participants to be used for the optimisation of the procedures and the materials. Lastly, it will allow a certain degree of precision in calculating standard deviations for the secondary outcomes that will be the key design parameters for the main study [49].

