### Recruitment

Potential participants will be recruited from outpatient clinics at the two hospitals. They will be identified and approached by a member of the clinical team. Bright colour reminders will be attached at the cover of the patient notes before their appointment to enhance consultants’ engagement with recruitment. After initial screening from the clinician, and if the patient is willing to hear about the study, following verbal consent, the patient will be introduced to the researcher attending the clinic for final screening and a detailed discussion of the study. All participants will need to consent for themselves following standard procedures (Additional file 3). We expect to recruit on average 1.07 participants per week per hospital during the 30-week recruitment period to reach our target.

The clinical teams in the two hospitals will also identify potential participants who have been treated in the two recruitment sites but have been followed up at local sites. Following the General Practitioner’s verification that the participants are alive, invitation letters signed by the consultant will be sent to these women, along with the participant information sheet, an opt-in form, the barriers to participation survey [50], and a business reply envelope.

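### Recruitment has three success rules of unequal strictness; the one called the main criterion sits at the design alternative, and the protocol does not say which rule decides

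*Protocol article*

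**What the plan says.** The protocol article sets a success rule for recruitment in three places.

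- **Primary outcome measures:** "The main criterion to judge the pilot study successful and a large-scale RCT feasible using the recruitment measure is recruiting (consenting) 30" per cent of eligible participants. The same sentence gives this as a count: "32 participants per 110 estimated to be eligible in each centre during the 6-month recruitment".
- **Sample size:** "a success rate of approximately 30" per cent or more is desirable, and "A success rate of 15" per cent or less is unacceptable. These become the alternative and the null of a one-stage exact test at a 5% "level of significance and 90" per cent power, for which "64 participants are needed so that we can estimate whether the percentage of participants with successful recruitment is" at or below 15% or at or above 30%. The cut-off is: "If we can recruit 15 or more participants, we can reject the null hypothesis". The section adds that a trial of this size allows the decision on a Phase III trial.
- **Statistical methods:** recruitment is reported with a 95% confidence interval, and the target is a lower limit of 15% or more.

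The recruitment period also appears twice. It is 6 months in the main criterion. Under Recruitment it is "1.07 participants per week per hospital during the 30-week recruitment period to reach our target".

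**The concern.** A one-stage design has a rate worth ruling out and a rate hoped for, and its cut-off on the observed rate lies between them. Here that cut-off is 23.4%, between 15% and 30%. The main criterion moves the cut-off up to the hoped-for rate itself. A trial that truly performs as hoped then falls on either side of the line largely by chance, and the 90% power quoted under Sample size does not describe that rule.

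Both the main criterion and the test are presented as the basis for going on to the large trial. Where they disagree, the feasibility verdict on a primary outcome depends on which section is read, and the choice could be made after the result is known.

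**Working it through.** **Inputs.** From Sample size: null rate 0.15, alternative 0.30, one-sided 5%, power 90%, n = 64, cut-off 15. From Primary outcome measures: 32 per 110 in each centre, so 64 of 220 over two centres. From Statistical methods: lower 95% limit of at least 15%. From Recruitment: 1.07 per week per hospital for 30 weeks. All probabilities are exact binomial tails, P(X ≥ r | n, p).

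**1. The protocol's own design.** P(X ≥ 15 | 64, 0.15) = 0.049 and P(X ≥ 15 | 64, 0.30) = 0.903. A search for the smallest n with one-sided error at most 0.05 and power at least 0.90 returns n = 64 with cut-off 15. The stated design is reproduced. Its chance of missing at a true 30% is 1 − 0.903 = 0.097.

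**2. The main criterion at a true rate of 30%.**

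| Reading | Rule | P(met) | P(missed) |
|---|---|---|---|
| Bracketed count, pooled | ≥ 64 of 220 (29.1%) | 0.640 | 0.360 |
| Literal 30%, pooled | ≥ 66 of 220 | 0.525 | 0.475 |
| Bracketed count in both centres | ≥ 32 of 110, twice | 0.618² = 0.381 | 0.619 |

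The last row takes the centres as independent with the same true rate.

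**3. The other two rules at 220 eligible.** The test is stated for a denominator of 64, but the rate is expected to be observed on about 220 eligible women. I therefore apply the same hypotheses at 220.

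- Rejection of 15% at one-sided 5%: P(X ≥ 43 | 220, 0.15) = 0.040 and P(X ≥ 42 | 220, 0.15) = 0.058, so the cut-off is 43 (19.5%). P(X ≥ 43 | 220, 0.30) exceeds 0.999.
- Exact two-sided 95% lower limit, the 0.025 quantile of Beta(x, n − x + 1): 14.9% at 44 of 220 and 15.3% at 45 of 220, so the cut-off is 45 (20.5%).

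**4. Where the rules disagree.** From 45 to 63 consents of 220 (20.5% to 28.6%), 15% is rejected and the confidence-limit target is met. The main criterion is missed on every reading above, since each needs at least 64 in total.

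The test and the confidence-limit target also differ slightly from each other. At 15 of 64 the test rejects, but the exact lower limit is 13.8%. At 220 the gap is 43 against 45.

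**5. Recruitment window.** 1.07 × 30 × 2 = 64.2, so the pace agrees with 64 over 30 weeks. Taking 6 months as 26 weeks, 1.07 × 26 × 2 = 55.6. Reaching 32 per hospital in 26 weeks needs 32/26 = 1.23 per week. The recruits are thus planned over a longer period than the one over which eligible women are counted.

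**The case against.** A target at the desired rate, set beside a test that rules out an unacceptable rate, is not in itself an error. The protocol nowhere claims 90% power for the main criterion; that figure belongs to 15 of 64. The Discussion grades the outcome in four categories, so missing 30% while excluding 15% need not mean a finding of non-feasible. This stands as a caution against calling the main criterion a simple pass or fail. It does not remove the conflict: the four categories are not tied to any recruitment rate, one rule is labelled the main criterion, and another is said to allow the Phase III decision.

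Three stronger readings are tempting and are not supported.

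- A reader might infer that the trial's own target of 64 of 220 fails its main criterion, because 64/220 = 29.1%. The same sentence defines its 30% as 32 per 110, and Sample size says approximately, so 64 of 220 meets the criterion on the document's own terms. A literal 30% would be 33 of 110; the difference is rounding.
- A reader might infer that a true 30% trial fails about half the time. That holds for the literal 66 of 220. Across the three readings the figure runs from 36% to 62%.
- A reader might scale the eligible pool to 30 weeks, 110 × 30/26 = 127 per centre, and conclude that the expected rate is 32/127 = 25%. This assumes a constant flow of eligible women. The inclusion criteria take anyone diagnosed in the previous 36 months, and women followed locally are invited by letter, so part of the pool already exists and does not grow with weeks. The 25% should not be used.

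**Conclusion.** The concern holds as a conflict between stated decision rules. Recruitment has three unreconciled criteria, and the one called the main criterion is at the design alternative. At a true rate of 30% it is missed 36%, 47% or 62% of the time, depending on the reading, against about 10% for the rule under Sample size. At 220 eligible there is a band of 19 possible results, 45 to 63 consents, in which the sections disagree. The 6-month and 30-week periods are a smaller but real mismatch.

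The figures rest on the protocol's estimate of 220 eligible women, binomial variation with a common rate, an exact two-sided interval for the confidence-limit rule, and independence of centres for the 62%. The sample size calculation itself is correct as stated. This should be settled before results are seen; it does not invalidate the trial.

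**What to change.** Name one deciding rule for recruitment and state its operating characteristics at the expected number of eligible women, about 220. Which rule governs is for the investigators. There are two coherent options.

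1. **Rejection of 15% decides, and 30% is labelled the desired rate.** At 220 eligible the cut-off is 43 consents at one-sided 5%, or 45 if the exact two-sided 95% lower limit is used; choose one of the two. State the downside: this can declare recruitment successful at 43, which is 64 − 43 = 21 short of the recruits wanted.
2. **30% remains the main criterion.** State whether it is pooled or per centre and as which count, and that its chance of being met at a true 30% is about 38% to 64% by reading, not 90%. Describe the test and the confidence limit as supporting.

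Under either option, say how the result feeds the four outcome categories in the Discussion. Give one recruitment window, so that recruits and eligible women are counted over the same period, with the weekly pace to match. Write 29%, or 33 per 110, where the count and the percentage appear together.

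The cost is protocol wording only. No further participants are needed.

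### The main recruitment criterion puts the pass mark at the alternative hypothesis (30 %), so the stated 90 % power does not apply to it, and the article does not say which recruitment rule governs

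*Protocol article*

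**What the plan says.** Primary outcome measures (protocol article) sets the success criterion for recruitment: "The main criterion to judge the pilot study successful and a large-scale RCT feasible using the recruitment measure is recruiting (consenting") 30 % of those eligible. The parenthesis that follows puts this in counts: "32 participants per 110 estimated to be eligible in each centre during the 6-month recruitment". The next sentence calls the figure a target. There are two centres (Study setting: "Participants will be recruited from two major academic hospitals in London"), so the counts pool to 64 of an estimated 220.

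Sample size treats the same outcome as a hypothesis test, "using A’Hern’s approach for one-stage phase II trials". There, "a success rate of approximately 30 % or more would be desirable for the trial to be considered feasible", and "A success rate of 15 % or less would be unacceptable". These become H1 (30 % or more) and H0 (15 % or less). The section continues "With a 5 % level of significance and 90 % power, 64 participants are needed" and gives the decision rule: "If we can recruit 15 or more participants, we can reject the null hypothesis". It adds that a trial of this size is enough to decide on moving to Phase III.

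Statistical methods gives 15 % as the target for the lower 95 % confidence limit of the recruitment rate. The Discussion lists four possible outcomes of the pilot: feasible unchanged, feasible with close monitoring, feasible with modifications, and not feasible. It attaches no recruitment rate to any of them.

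**The concern.** In a single-stage design the alternative is the rate at which the trial should usually succeed. The pass mark therefore has to lie between the null and the alternative, and 15 of 64 (23.4 %) does lie between 15 % and 30 %. If the alternative itself becomes the observed pass mark, a trial whose true rate equals the alternative reaches it only a little more than half the time. Primary outcome measures does this, and calls the result the main criterion.

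Two sections thus each claim to decide whether recruitment succeeded, on the outcome that sized the trial. They use different marks, and no sentence ranks them. A reader who carries the 90 % over to the main criterion will be misled about how often a pilot recruiting at the hoped-for rate would meet it. An observed rate of, say, 26 % could be reported as success under one section and as a miss under the other. The choice between them would then be made after the result is known.

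**Working it through.** **Inputs.** From Sample size: p0 = 0.15, p1 = 0.30, significance 5 %, power 90 %, n = 64, cut-off 15. From Primary outcome measures: 30 % of eligible women, 32 per 110 in each centre. From Study setting: two centres, so 2 × 32 = 64 and 2 × 110 = 220.

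**Formula.** With X ~ Binomial(n, p), the chance of reaching a mark r is P(X ≥ r | n, p).

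**Step 1: reproduce the stated design.**
- P(X ≥ 15 | 64, 0.15) = 0.049, the one-sided type I error.
- P(X ≥ 15 | 64, 0.30) = 0.903, the power.
- No smaller n has an exact one-sided error of at most 0.05 with power of at least 0.90.

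The stated n, cut-off, level and power are right for this rule.

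**Step 2: express the main criterion in counts.** 32/110 = 64/220 = 29.1 %. A literal 30 % is 0.30 × 110 = 33 per centre, or 0.30 × 220 = 66 in all.

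**Step 3: chance of meeting each mark when the true rate is 30 %.**

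| Rule | Observed rate needed | P(met) | P(missed) |
|---|---|---|---|
| Sample size: 15 of 64 | 23.4 % | 0.903 | 0.097 |
| Main criterion, stated counts: 64 of 220 | 29.1 % | 0.640 | 0.360 |
| Main criterion, literal 30 %: 66 of 220 | 30.0 % | 0.525 | 0.475 |

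**Step 4: does this depend on the 220?** If recruitment closed at 64 after 213 eligible women, 64/213 = 30.05 %, and P(X ≥ 64 | 213, 0.30) = 0.52. With 64 as the denominator, 19 of 64 (29.7 %) is reached with probability 0.57 and 20 of 64 (31.3 %) with probability 0.46. None of these comes near 0.90.

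**Step 5: what true rate would give the main criterion a 90 % chance of being met?** About 33 % for 64 of 220 (P = 0.905 at 0.33) and about 34 % for 66 of 220 (P = 0.908 at 0.34).

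**Step 6: where the rules disagree.** Taking the plan's own cut-off as a rate, observed values from 23.4 % up to just under 29–30 % reject 15 % but miss the main criterion.

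**The case against.** The best defence is that 30 % is the target for full success, 15 % is the floor, and the Discussion's four verdicts cover what lies between. Some wording supports this. Primary outcome measures calls 30 % a target in its second sentence, Sample size calls about 30 % desirable, and Statistical methods uses 15 % for the confidence limit. A target stricter than a test cut-off is a legitimate, cautious choice, and Primary outcome measures claims no power for it.

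Much of this stands, and it rules out several stronger readings:

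- A reader might infer that a truly feasible trial would be wrongly rejected four to five times in ten. The documents do not support that. They nowhere say that missing 30 % means non-feasible, and intermediate verdicts exist.
- A reader might infer that full recruitment of 64 can never reach 30 % because 64/220 is 29.1 %. But 220 is an estimate, and 64 of 213 would exceed 30 %.
- The words about each centre might be read as requiring both centres to pass separately. The article states no such rule.
- The gap between 29.1 % and 30 % is rounding, given that Sample size speaks of approximately 30 %.

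The defence does not remove the conflict. The sentence explicitly makes 30 % the main criterion for success and feasibility, Sample size gives its own test as the basis for proceeding to Phase III, and the Discussion ties no verdict to a rate. A fuller analysis plan might add that link, but two conflicting rules already stated in the article are not an omitted detail.

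**Conclusion.** The point holds at moderate severity. The article gives two different recruitment rules without saying which one governs. The 90 % power is correct for the rule in Sample size (0.903) but is not a property of the criterion called main. At a true 30 %, that criterion is met with probability about 0.64 on the stated counts and 0.53 if 30 % is taken literally, so it is missed about 36 % of the time and at most about 47 %.

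These figures assume independent consent decisions at a common rate and exactly 220 eligible women, which is the article's own estimate. The conclusion does not depend on that exact number. No participant, measurement or analysis model is affected. What is affected is the conclusion the pilot may draw about recruitment.

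**What to change.** State one governing rule for recruitment, with eligible women as its denominator and its own error rates. Either of two versions would do:

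1. Make the test against 15 % decisive and call 30 % the planning rate. Assign results that reject 15 % but fall below 30 % to the Discussion's verdicts of close monitoring or of protocol modifications. Recompute the cut-off for the eligible denominator. As an illustration only, since the article contains no such rule, an exact one-sided 5 % test on 220 has cut-off 43 (19.5 %), type I error 0.040 and power above 0.999 at 30 %.
2. Keep 30 % as the pass mark, and state that its chance of being met at a true 30 % is about 53–64 %, not 90 %.

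As a minor correction, align the parenthesis: 32 per 110 is 29 %, and 30 % of 110 is 33.

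The cost is wording in Primary outcome measures, Sample size and the Discussion, with no extra participants or data. Trial status says recruitment is already under way, so the rule should be fixed before the recruitment result is examined.
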